### Power calculation

The sample size was informed by previous studies applying tDCS in populations with cognitive impairment. For example, Khedr et al. administered active and sham tDCS to the left DLPFC over 10 consecutive days in 34 participants (Khedr et al., 2014). Additionally, the same group has shown efficacy of tDCS with the anode (positive electrode) placed at the T3-P3 or T4-P4 in 46 AD patients (Khedr et al., 2019).

Based on these precedents, and assuming a medium effect size (Cohen’s d ≈ 0.5–0.6) as reported in prior MCI/AD and motor adaptation studies, we calculated that a minimum of 50 participants per group would be required to achieve 90% power (1–*β* = 0.9) at a two-tailed *α* = 0.05. To allow for an anticipated dropout rate of approximately 20%, we increased the target to 60 participants in each diagnostic group (AD-MCI and PD-MCI), yielding a total sample of 120 participants. This sample size ensures sufficient power to detect clinically meaningful differences in cognitive outcomes between stimulation conditions.

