**Figure 1 fig1:**
[figure not shown]
Study design and group allocation. Flowchart illustrating the study design for participants meeting inclusion criteria. Initial neurocognitive assessments, EEG, and fMRI were performed on 60 individuals with aMCI and 60 with PD-MCI. Participants were randomized in a 1:1 ratio to receive tDCS targeting either the DLPFC or the LPC. Within each stimulation arm, participants were further randomized in a 2:1 ratio to the Real or Sham tDCS condition, yielding 20 aMCI and 20 PD-MCI (real) versus 10 aMCI and 10 PD-MCI (sham). Created with BioRender.com.

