This study has some limitations. Firstly, despite large number of participants, given the multiple groups, it is a small-scale prospective study necessitating a study with a larger number per group to substantiate the clinical efficacy. Secondly, the small number of sessions and indirect stimulation of hippocampal circuits, along with the heterogeneity caused by clinical presentation due to different diseases (PD-MCI and AD-MCI), limit the generalizability of our findings. It is also worth discussing our study design, which proposes shorter courses of tDCS application compared to the previous literature. Herein, our design was principally based on the literature demonstrating that shorter interventions can also be effective, allowing us to optimize the balance between scientific rigor and patient adherence. In that context, while some studies have used longer protocols (20–30 sessions), there is also solid evidence that shorter courses ranging between one and 10 sessions (Khedr et al., 2019; Rasmussen et al., 2021; Smirni et al., 2021) can already produce meaningful cognitive and neural improvements (Prathum et al., 2025). For instance, Smirni et al. have shown recovery on phonemic fluency performance even after one session (Smirni et al., 2021) while Kehdr et al. have shown the improvement of cognitive test scores after 10 sessions of tDCS over 2 weeks (Khedr et al., 2019). The impact of shorter courses of tDCS on cognitive functions was suggested with the following study by Rasmussen et al. showing that 6 sessions (3 sessions/day, 2 days) was effective on delayed memory impairment in patients with AD (Rasmussen et al., 2021).

We therefore selected 10 days over 14 days as a practical and participant-friendly schedule, which is easier for patients to complete, helps minimize dropout, and makes the intervention more feasible in real-world clinical settings.

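### The stated 90% power is counted on a whole diagnosis (50, raised to 60) but claimed for real versus sham, which is 40 versus 20 at most within a diagnosis and does not reach it

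*Protocol article*

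**What the plan says.** The Power calculation section fixes four inputs: an effect ("assuming a medium effect size (Cohen’s d ≈ 0.5–0.6"), the error rate ("at a two-tailed *α* = 0.05"), 90% power, and a dropout of about 20%. It gives the result as "we calculated that a minimum of 50 participants per group would be required to achieve 90% power".

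It then says which group it means: "we increased the target to 60 participants in each diagnostic group (AD-MCI and PD-MCI), yielding a total sample of 120 participants". It closes by attaching the power to a different comparison: "This sample size ensures sufficient power to detect clinically meaningful differences in cognitive outcomes between stimulation conditions".

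The Figure 1 legend describes the split inside each target: "participants were further randomized in a 2:1 ratio to the Real or Sham tDCS condition". It gives 20 real and 10 sham patients per diagnosis and target, so 40 real and 20 sham per diagnosis. The Statistical analyses section runs the models separately by diagnosis first, with real versus sham and target as between-subject factors. Diagnosis enters as a factor only afterwards.

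The limitations paragraph of the Discussion says that "given the multiple groups, it is a small-scale prospective study necessitating a study with a larger number per group to substantiate the clinical efficacy".

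**The concern.** The unit counted and the unit compared differ. Fifty or sixty is the size of a diagnosis. The claim is about real versus sham, and inside a diagnosis the smaller arm has 20 patients, or 10 within one target.

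This section is the only justification given for the sample size. If a sham-controlled result is null, a reader who accepts the 90% figure will take it as fair evidence that an effect of 0.5 to 0.6 SD is absent. The trial may well have missed such an effect. The limitations paragraph also says the opposite of the power paragraph, so the article supports two readings of the same result.

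**Working it through.** **Inputs.** From the Power calculation section: d = 0.5 to 0.6, two-sided α = 0.05, 90% power, 50 raised to 60 per diagnosis, 20% dropout. From Figure 1 and the Participants section: 2:1 real to sham within each target. Dropout is assumed equal across arms.

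**Formula.** For n₁ real and n₂ sham patients, the noncentrality is δ = d × √(n₁n₂/(n₁+n₂)). Power is the probability that a noncentral t with n₁+n₂−2 degrees of freedom and noncentrality δ exceeds the two-sided 5% critical value.

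**Step 1: the plan's own figure.** Taking the group as an arm:
- 50 versus 50 gives √(2500/100) = 5, so δ = 2.5 to 3.0 and power is 70% to 84%.
- 90% power needs 86 per arm at d = 0.5, 71 at 0.55 and 60 at 0.6.
- 50 per arm reaches 90% only at d of about 0.65, outside the stated range.

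The figure is not reproduced on this reading.

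**Step 2: the arms as randomised, unadjusted.**

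| Comparison | n real : n sham | δ at d = 0.5, 0.6 | Power | Detectable d at 90% |
|---|---|---|---|---|
| Within a diagnosis, all retained | 40 : 20 | 1.83, 2.19 | 44–58% | 0.90 |
| Within a diagnosis, after 20% dropout | 32 : 16 | 1.63, 1.96 | 36–48% | 1.01 |
| Within a diagnosis and target, all retained | 20 : 10 | 1.29, 1.55 | 24–32% | 1.30 |
| Pooled over diagnosis and target, all retained | 80 : 40 | 2.58, 3.10 | 73–87% | 0.63 |
| Pooled, after 20% dropout | 64 : 32 | 2.31, 2.77 | 63–78% | 0.71 |

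**Step 3: crediting baseline adjustment.** The article states no correlation, so a range is assumed. Adjusting for baseline with correlation ρ replaces d by d/√(1−ρ²).

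| Assumed ρ | Multiplier | 40 : 20 | 32 : 16 |
|---|---|---|---|
| 0.5 | 1.155 | 55–70% | 45–60% |
| 0.7 | 1.400 | 71–86% | 61–77% |
| 0.8 | 1.667 | 85–95% | 76–89% |

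After the planned dropout, no row reaches 90% anywhere in the stated effect range.

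**Step 4: the interaction.** The planned contrast named in the Statistical analyses section is Group × Target × Time. For a difference between targets of 0.5 to 0.6 SD in the real-minus-sham effect, the standard error is √(2 × (1/20 + 1/10)) = 0.548. Unadjusted power by normal approximation is about 15–19%.

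**Step 5: dropout.** 50/(1 − 0.20) = 62.5, so 63 are needed. Sixty less 20% leaves 48, below the stated minimum of 50.

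**The case against.** The strongest defence is that 50 per diagnosis may come from the repeated-measures model the trial plans. A within-between F test with four equal cells, three visits, f = 0.25 and a correlation of 0.5 first reaches 90% at a total of 50 patients (power 0.902). That stands as a possible origin. A reader might infer that 50 could suffice only for a before-after test within one group; this calculation shows that inference to be wrong. It does not rescue the claim. The article states none of these parameters, the real cells are 2:1, and an overall F test of four cells over time is not 90% power for real versus sham at d of 0.5 to 0.6.

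Second, a t-test on one time point is not the planned analysis, which uses three visits and covariates. That stands too, so 44–58% is the unadjusted figure and not the power of the planned model. More favourable assumptions come close. Suppose both post-baseline visits are averaged, adjusted for baseline, and all correlations are 0.8. The residual SD is then √(0.9 − 0.64) = 0.51, and power is 94–99% at 40:20 but 88–96% at 32:16. Even here d = 0.5 falls short after dropout, and the article names neither the averaging nor the correlation.

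Third, two tempting readings go too far:
- One is that there are two separate errors, in the per-arm arithmetic and in the unit counted. The text defines the group as a diagnosis, so the per-arm calculation only tests an alternative reading of the same sentence.
- The other is that true power is half the stated figure or less. Unadjusted power at 40:20 is 44–58%, and adjustment or pooling raises it.

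Finally, the limitations paragraph does warn readers. That softens the harm, but it contradicts the power paragraph and does not correct it.

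**Conclusion.** The concern holds. The 90% figure is attached to the number of patients in a diagnosis and is not delivered for real versus sham within a diagnosis across d = 0.5 to 0.6. Unadjusted power is 44–58% with everyone retained and 36–48% after dropout. With single-visit baseline adjustment at correlations of 0.5 to 0.8 it is 45–89% after dropout.

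These figures assume two-sided 0.05, equal dropout across arms, and d on the scale of the unadjusted outcome SD. The exact shortfall depends on a test and a correlation the article does not give. The mismatch between the unit counted and the comparison claimed does not depend on them. This must be corrected, because it is the only stated basis for the sample size.

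**What to change.** Keep 120 patients and rewrite the power paragraph.

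1. Replace the 90% statement with the power, or detectable d, of real versus sham at 2:1 within a diagnosis after dropout. Name the test and the assumed correlation and show a range. The unadjusted entry would be 36–48%, with a detectable d of about 1.0.
2. Delete the closing sentence on sufficient power, so that the paragraph agrees with the limitations.
3. State that the per-target and Group × Target × Time contrasts have lower power and will be reported as estimates with confidence intervals.
4. State that the best-powered sham comparison is the one pooled over diagnosis and target: 80 versus 40, unadjusted 73–87%, or 63–78% after dropout.
5. Correct the dropout line: 60 randomised leaves 48 per diagnosis.

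The cost is a short rewrite and a less favourable stated power. No extra patients are needed.

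### Sixty patients per diagnosis with 20% dropout leaves 48 evaluable, two short of the plan's own minimum of 50

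*Protocol article*

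**What the plan says.** The sample size rests on three figures, all in the Power calculation section of the protocol article.

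- **Minimum:** "we calculated that a minimum of 50 participants per group would be required to achieve 90% power", "at a two-tailed *α* = 0.05".
- **Dropout:** "To allow for an anticipated dropout rate of approximately 20"%.
- **Target:** "we increased the target to 60 participants in each diagnostic group (AD-MCI and PD-MCI), yielding a total sample of 120 participants".

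The section closes by saying that this size gives sufficient power to compare stimulation conditions. So 60 is presented as the enrolment that keeps 50 patients per diagnosis after the expected loss. The article gives no inflation formula, no second dropout figure and no rule for replacing patients who leave.

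The caption of Figure 1 gives the allocation that decides how any loss falls on the arms. Each diagnosis is split 1:1 by target, and then "Within each stimulation arm, participants were further randomized in a 2:1 ratio to the Real or Sham tDCS condition". With 60 patients, that is 40 real and 20 sham per diagnosis.

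**The concern.** A dropout rate is a proportion of the patients enrolled. To finish with n evaluable patients when a fraction d is lost, enrolment must be n/(1 − d). Multiplying by (1 + d) instead always gives too few, because (1 − d)(1 + d) = 1 − d², which is below 1. With d = 0.20, the evaluable number is 96% of the intended number.

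The target of 60 is exactly what the multiplication gives. If so, the trial falls below its own minimum under its own dropout assumption, and the reassurance about power rests on a number the plan does not expect to reach. If the power calculation is reworked on a larger base and the same multiplier is used, the 4% shortfall carries over.

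**Working it through.** **Inputs**, all from the Power calculation section except the last:

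- minimum evaluable per group, n = 50
- dropout, d = 0.20 (stated as approximate)
- enrolment target per diagnosis = 60, total 120
- two-sided α = 0.05 and Cohen's d of 0.5 to 0.6, used only to size the effect
- real to sham 2:1 within each target (Figure 1 caption)

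The 50 is compared with a whole diagnosis because the article's own sentence does so.

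**Step 1. Reproduce the printed target.** n × (1 + d) = 50 × 1.2 = 60. This matches exactly.

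**Step 2. Apply the standard inflation.** n/(1 − d) = 50/0.80 = 62.5, rounded up to 63 per diagnosis and 126 in total. This does not reproduce 60.

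**Step 3. Evaluable patients from 60 enrolled.** 60 × (1 − 0.20) = 48 per diagnosis and 96 in total, against the intended 50 and 100.

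**Step 4. Dropout that 60 can absorb.** 1 − 50/60 = 0.167.

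| Dropout | Evaluable from 60 | Enrolment needed to keep 50 |
|---|---|---|
| 15% | 51.0 | 58.8 |
| 16% | 50.4 | 59.5 |
| 17% | 49.8 | 60.2 |
| 18% | 49.2 | 61.0 |
| 20% | 48.0 | 62.5 |
| 25% | 45.0 | 66.7 |

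**Step 5. What 48 means by arm.** If loss is proportional, 40 real and 20 sham become 32 and 16. The article does not say how loss will divide between arms, so proportional loss is an assumption.

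**Step 6. Cost in power.** For two arms of sizes n₁ and n₂, the normal approximation is power = Φ(d·√[n₁n₂/(n₁ + n₂)] − 1.96), where d is now Cohen's d. The planned model is a covariate-adjusted repeated-measures analysis, so these figures are only a guide.

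| Real : sham in one diagnosis | √[n₁n₂/(n₁ + n₂)] | Power at d = 0.5 | Power at d = 0.6 |
|---|---|---|---|
| 40 : 20 (60 enrolled, no loss) | 3.651 | 44.7% | 59.1% |
| 33.3 : 16.7 (50 evaluable) | 3.333 | 38.5% | 51.6% |
| 32 : 16 (48 evaluable) | 3.266 | 37.2% | 50.0% |

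The slip itself is the difference between the last two rows: 1.3 points at d = 0.5 and 1.6 points at d = 0.6. Reading 50 and 48 as the size of each of two equal arms gives a similar loss (noncentral t: 69.7% against 67.9% at d = 0.5, and 84.4% against 82.9% at d = 0.6).

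None of these figures is near 90%. That gap comes from the base of 50 and from applying it to a diagnosis that contains both real and sham patients. It is a separate matter, and correcting the dropout step would not close it.

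**The case against.** The strongest reply is that this hardly matters. The dropout figure is stated as approximate, 60 tolerates 16.7%, the gap is two patients per diagnosis, and the loss of power is one to two points. The article's limitations paragraph already calls the study small given its number of groups. The larger weakness is the base of 50, and correcting its inflation alone could suggest that the rest of the calculation is sound. All of this is fair on size, and it is why the point is minor. It does not reconcile the figures: 60 fails at the plan's own central value of 20% and at anything from 17% upward.

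The formula is also not printed, so 50 × 1.2 is an inference from an exact match. Sixty might have been chosen because it divides cleanly into 30 and 30 by target and then 20 and 10 by arm. That stands as a caution about the cause. The shortfall of 48 against 50 does not depend on it.

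Third, 63 does not fit the allocation. Even division needs a multiple of six, so a recruitment remedy would mean 66 per diagnosis and 132 in total. This is correct, and it is a reason to restate the figure rather than add patients.

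Fourth, a sham arm of 16 is mainly the result of 2:1 allocation and the assumed loss. With 63 enrolled it would be about 21 × 0.80 = 16.8, so less than one sham patient per diagnosis is due to the slip. The 16 should be read as the expected arm size, not as the damage done by this error.

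Finally, a fuller protocol might contain a replacement rule. The article neither states nor implies one, and it presents 60 as sufficient in itself.

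**Conclusion.** The point holds, and it is minor. On the article's own figures, 60 enrolled per diagnosis yields 48 evaluable at 20% dropout, against a stated minimum of 50: two short per diagnosis and four in the trial. Sixty is enough only if dropout is 16.7% or less. Keeping 50 at 20% would need 63 per diagnosis, or 66 for even allocation.

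This assumes that the 20% is a proportion of those enrolled, that lost patients are not replaced, and that 50 is meant as the evaluable number per diagnosis. The effect on power is one to two percentage points. No endpoint or analysis changes.

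**What to change.** Replace the sentence on dropout in the Power calculation section. No patients need be added and the design stays as it is. Either of these statements would be correct:

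- 60 per diagnosis is expected to give 48 evaluable patients at 20% dropout, about 32 real and 16 sham if loss is proportional; or
- 60 per diagnosis keeps the minimum of 50 provided dropout does not exceed 16.7%.

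Then quote power at 48 evaluable patients and name the comparison it refers to, such as real against sham within one diagnosis at 32 and 16. A figure for 48 without that split would not inform the planned contrasts. If the base of 50 is recalculated, use division by (1 − 0.20) for the new inflation.

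The cost is one sentence and a slightly less favourable stated figure.

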## Discussion

Our hypothesis, which aims to determine whether region-specific tDCS may exert significant pro-cognitive effects when applied during the early stages of Parkinson’s and Alzheimer’s dementia, is deserving of mention given the existing literature on the effects of tDCS. Herein, there is valuable data that discusses the influence of tDCS on cognition in both healthy and pathological conditions, emphasizing principally the importance of stimulation location and disease stage (i.e., PD-MCI or AD-MCI).

Numerous studies imply that MCI is a common intermediate stage for the development of various types of dementia. One advantage of this shared stage is the potential to offer a two-for-one strategy that could benefit from novel neuromodulating methods such as tDCS, which may be essential for filling an inevitable gap in the early management of progressive dementia diseases. tDCS application over DLPFC has been already shown to augment functional connectivity between DMN and frontoparietal regions while simultaneously causing decreased DMN activity during the performance of a cognitive task associated with relevant resting EEG changes (Marceglia et al., 2016; Vulić et al., 2021) that resulted in improved motor and cognitive functions (Brak et al., 2022; Ferrucci et al., 2008). Furthermore, stimulation of temporoparietal regions resulted in enhanced performance in memory and global cognitive functions (Park et al., 2019), leading to a comparable level of improvements obtained from pharmacological treatment using cholinesterase inhibitors (Ferrucci et al., 2008; Khedr et al., 2019; Marceglia et al., 2016). These findings were suggested with fMRI studies with anodal tDCS showing considerably increased connectivity between DMN nodes (hippocampus, dorsal attention network, CN, salient network, and sensory-motor network) (Manenti et al., 2010, 2020), and increased segregation in DMN networks (Hunter et al., 2015).

In addition to the role of DMN, PMN seems to be a promising target for the diagnosis and treatment of cognitive impairment. Although PMN is anatomically and functionally adjacent to the DMN, evidence suggests its distinct role as a functional network consisting of parietal regions, cingulate, and the precuneus (Gilmore et al., 2015). Furthermore, in contrast to the DMN, which is more commonly implicated in self-referential, and mind wandering (Sestieri et al., 2011) accumulating evidence suggest that PMN is involved in specific cognitive functions such as episodic and associative memory processing (Hu et al., 2016). Hence, targeting the PMN might be a unique stimulation approach, especially when considering recent evidence that the PMN integrity is impaired in early stages of dementia development (Velioglu et al., 2021; Vulić et al., 2021).

In accordance with these findings, the restoration of impaired functional integrity between LPC and hippocampal regions resulted in an improved performance on recognition memory after repetitive magnetic stimulation (rTMS), in Alzheimer’s patients (Velioglu et al., 2021). These findings were aligned with tDCS stimulation of the posterior parietal cortex (PPC), resulting in improved performance that persisted even 5 days after stimulation (Vulić et al., 2021).

These results affirmed by the results of a recent meta-analysis covering more than 200 healthy subjects, suggesting that PPC (Galli et al., 2019) and PMN-targeted stimulation exerted considerably higher pro-cognitive effects than other application sites, which may be related to unique connectivity changes between the precuneus, lingual gyrus, and hippocampus in healthy subjects (Warren et al., 2019). Also, the following studies evaluating the effect of parietal stimulation through tDCS gave promising results. For instance, Zivanovic et al. have revealed that different types of tDCS applied on the parietal region revealed comparable beneficial effects on short term associative memory (Živanović et al., 2022). The role of tDCS on specific memory domains has been also suggested by a very recent study by healthy individuals showing that the stimulation of parietal cortices resulted in improved verbal memory associated with theta and alpha power changes on responsible brain regions (Arif et al., 2024).

This study has some limitations. Firstly, despite large number of participants, given the multiple groups, it is a small-scale prospective study necessitating a study with a larger number per group to substantiate the clinical efficacy. Secondly, the small number of sessions and indirect stimulation of hippocampal circuits, along with the heterogeneity caused by clinical presentation due to different diseases (PD-MCI and AD-MCI), limit the generalizability of our findings. It is also worth discussing our study design, which proposes shorter courses of tDCS application compared to the previous literature. Herein, our design was principally based on the literature demonstrating that shorter interventions can also be effective, allowing us to optimize the balance between scientific rigor and patient adherence. In that context, while some studies have used longer protocols (20–30 sessions), there is also solid evidence that shorter courses ranging between one and 10 sessions (Khedr et al., 2019; Rasmussen et al., 2021; Smirni et al., 2021) can already produce meaningful cognitive and neural improvements (Prathum et al., 2025). For instance, Smirni et al. have shown recovery on phonemic fluency performance even after one session (Smirni et al., 2021) while Kehdr et al. have shown the improvement of cognitive test scores after 10 sessions of tDCS over 2 weeks (Khedr et al., 2019). The impact of shorter courses of tDCS on cognitive functions was suggested with the following study by Rasmussen et al. showing that 6 sessions (3 sessions/day, 2 days) was effective on delayed memory impairment in patients with AD (Rasmussen et al., 2021).

We therefore selected 10 days over 14 days as a practical and participant-friendly schedule, which is easier for patients to complete, helps minimize dropout, and makes the intervention more feasible in real-world clinical settings.

Nevertheless, caution should be exercised when applying this procedure to patients with early cognitive impairment especially regarding the efficacy of tDCS, which may depend on the indirect nature of the stimulus that might not reach the hippocampus. Within that context, despite some positive results, including also our previous study (Velioglu et al., 2021), the inducibility of the hippocampus through stimulation of the parietal cortex target areas will be tested concerning dosages with varying intensities to achieve the optimal effect of tDCS on cognitive symptoms, alongside changes in hippocampal connectivity.

To sum up, considering its beneficial cognitive effects in healthy individuals, tDCS is not only advantageous for early intervention but also for understanding the ethology and pathogenesis of early stages of dementia such as in AD-MCI and PD-MCI, as it has the potential to provide a clearer link between neurostructural and functional pathologies and neurocognitive outcomes. The application of tDCS to unconventional regions, combined with detailed fMRI analyses, will yield new insights into the pathophysiology of these diseases.

